Participants will be questioned at enrollment about their functional status along with other baseline medical conditions such as co-morbidities using a standardized questionnaire. Functional status is the individual's ability to perform normal activities of daily living. We will use the index from the Vulnerable Elders Survey (7) along with individual elements from other indices and test their association with ARI to determine if experiencing ARIs or SARIs impacts functional status. Cognitive function will be self-assessed as other measures require trained medical personnel to implement. Vulnerable Elders Survey (VES-13) is a function-based questionnaire that was developed to screen elderly 65 years of age or greater in the community to determine their risk for health deterioration (7, 8). The questionnaire asks elderly to self-report their age, health, limitations in physical function and functional disabilities, and takes an average of less than five minutes to complete(7, 8). This tool can be administered over the phone or in person. Each response to each question on the form has a point value attached ranging from 0 to 3 points, and it is scored by adding up points based on the responses received, up to 10.(8) Scores  $\geq 3$  indicate frailty associated with increased mortality. The test has been shown to be reliable (7, 9, 10). The same functional status measurements were used in a companion study which assessed whether functional status correlated with obtaining flu vaccine and has already been translated into Thai. Using the same functional status measurement tool in this study will allow us to compare outcomes between both studies and build upon prior conclusions. Participants will be asked to re-take the functional status VES-13 questionnaire every six months during the study period to measure changes in functional status over time.

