| 4                                                                                                                                | In general, compared to other people your age, would you say that your health is poor, fair, good, very good or excellent? | 1 Very poor
2 Bad
3 Fair
4 Good
5 Very good or excellent
77 Do not know
99 Declined to answer |      |
| 5                                                                                                                                | Have you experienced any severe illness in the last year?                                                                  | 1 Yes
2 No
77 Do not know
99 Declined to answer                                                        |      |
| 6                                                                                                                                | Did you have to be hospitalized for any illness in the last year?                                                          | 1 Yes
2 No
77 Do not know
99 Declined to answer                                                        |      |

|                                                                                              |                                                                                                                                                                                                              |                                                                                                                                                                                      |                            |                          |                            |                          |                                                           |
|----------------------------------------------------------------------------------------------|--------------------------------------------------------------------------------------------------------------------------------------------------------------------------------------------------------------|--------------------------------------------------------------------------------------------------------------------------------------------------------------------------------------|----------------------------|--------------------------|----------------------------|--------------------------|-----------------------------------------------------------|

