|----|---------------------------------------------------------------------------------------------------------------------------------------------|------------------------------------------------------|----------------------------------------------------------------------------------------|
| 19 | Because of your health or a physical condition, do you have any difficulty managing money (like keeping track of expenses or paying bills)? | 1 Yes
2 No
3 Don't do
99 Declined to answer | If no or declines to answer, skip to 22

If 'don't do,' skip to 21 |
| 20 | If yes, do you get help with managing money?                                                                                                | 1 Yes
2 No
99 Declined to answer               | Skip to 22                                                                      |
| 21 | If you don't manage your money, is that because of your health?                                                                             | 1 Yes
2 No
99 Declined to answer               |                                                                                        |
| 22 | Because of your health or a physical condition, do you have any difficulty walking across the room?                                         | 1 Yes
2 No
3 Don't do
99 Declined to answer | If no or declines to answer, skip to 25

If 'don't do,' skip to 24 |
| 23 | If yes, do you get help with walking?                                                                                                       | 1 Yes
2 No                                        | Skip to 25                                                                      |

|    |                                                                                                                                                             |                                                      |                                                                                        |
|----|-------------------------------------------------------------------------------------------------------------------------------------------------------------|------------------------------------------------------|----------------------------------------------------------------------------------------|

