|    |                                                                                                                                                             | 99 Declined to answer                                |                                                                                        |
| 24 | If you can't walk across the room, is that because of your health?                                                                                          | 1 Yes
2 No
99 Declined to answer               |                                                                                        |
| 25 | Because of your health or a physical condition, do you have any difficulty doing light housework (like washing dishes, straightening up or light cleaning)? | 1 Yes
2 No
3 Don't do
99 Declined to answer | If no or declines to answer, skip to 28

If 'don't do,' skip to 27 |
| 26 | If yes, do you get help with light housework?                                                                                                               | 1 Yes
2 No
99 Declined to answer               | Skip to 28                                                                      |
| 27 | If you can't do light housework, is that because of your health?                                                                                            | 1 Yes
2 No
99 Declined to answer               |                                                                                        |
| 28 | Because of your health or a physical condition, do you have any difficulty bathing or showering?                                                            | 1 Yes
2 No
3 Don't do
99 Declined to answer | If no or declines to answer, skip to 31                                         |

|    |                                                                                                                  |                                                                                                                                                                                             |                                  |

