|    |                                                                                                                                                              |                                                      |                                                                                        |
|----|--------------------------------------------------------------------------------------------------------------------------------------------------------------|------------------------------------------------------|----------------------------------------------------------------------------------------|
| 16 | If yes, do you get help with managing money?                                                                                                                 | 1 Yes
2 No
99 Declined to answer               | Skip to 18                                                                      |
| 17 | If you don't manage your money, is that because

of your health?                                                                                       | 1 Yes
2 No
99 Declined to answer               |                                                                                        |
| 18 | Because of your health or a physical condition, do you have any difficulty walking across the room (using a cane or walker is okay)?                         | 1 Yes
2 No
3 Don't do
99 Declined to answer | If no or declines to answer, skip to 21

If 'don't do,' skip to 20 |
| 19 | If yes, do you get help with walking?                                                                                                                        | 1 Yes
2 No
99 Declined to answer               | Skip to 21                                                                      |
| 20 | If you don't walk across the room, is that because

of your health?                                                                                    | 1 Yes
2 No
99 Declined to answer               |                                                                                        |
| 21 | Because of your health or a physical condition, do you have any difficulty doing light housework (like washing dishes, straightening up, or light cleaning)? | 1 Yes
2 No
3 Don't do                          | If no or declines to answer,                                                    |

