|    |                                                                                                  |                                                                  |                                                                                        |
|----|--------------------------------------------------------------------------------------------------|------------------------------------------------------------------|----------------------------------------------------------------------------------------|
|    |                                                                                                  | 99 Declined to answer                                            | skip to 24

If 'don't do,' skip to 23                              |
| 22 | If yes, do you get help with light housework?                                                    | 1 Yes

2 No

99 Declined to answer                   | Skip to 24                                                                      |
| 23 | If you don't do light housework, is that because of your health?                                 | 1 Yes

2 No

99 Declined to answer                   |                                                                                        |
| 24 | Because of your health or a physical condition, do you have any difficulty bathing or showering? | 1 Yes

2 No

3 Don't do

99 Declined to answer | If no or declines to answer, skip to 27

If 'don't do,' skip to 26 |
| 25 | If yes, do you get help with bathing or showering?                                               | 1 Yes

2 No

99 Declined to answer                   | Skip to 27                                                                      |
| 26 | If you don't bathe or shower, is that because of your health?                                    | 1 Yes

2 No

99 Declined to answer                   |                                                                                        |

|                                                    |                                                                                                                  |                                                                                                                                                                                             |  |

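### The enrolment and follow-up functional-status forms word several items differently, so within-person change from an enrolment score can include a wording artefact

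*Protocol*

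**What the plan says.** Section 3.1.4 plans repeated measurement with one instrument: "Participants will be asked to re-take the functional status VES-13 questionnaire every six months during the study period". The stated aim is to follow change over time. Section 7.5.1 (secondary objective 2.1) compares changes between participants with a first ARI or SARI and matched controls. Section 7.5.2 matches on age, sex, vaccination and the most recent functional-status score, with the control interviewed at the same time as the case. Section 7.9 sets the score tolerance at 1 point.

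The appendix holds two forms. Enrolment form 4b, item 22, asks "do you have any difficulty walking across the room" and stops there. Follow-up form 4f, item 18, asks "do you have any difficulty walking across the room (using a cane or walker is okay".

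The sub-items put to people who answer that they do not do an activity also differ. On walking, 4b has "If you can't walk across the room, is that because of your health" and 4f has "If you don't walk across the room, is that because" of health. On housework, 4b has "If you can't do light housework, is that because of your health" and 4f has "If you don't do light housework, is that because of your health". Bathing changes in the same way. The top self-rated health code on 4b is "5 Very good or excellent"; on 4f the word excellent is dropped.

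**The concern.** A change score is interpretable only if the same question is put at both times. A participant who walks with a cane and is stable can truthfully report difficulty on 4b, where no aid is mentioned, and no difficulty on 4f, where an aid is allowed. That would be recorded as improvement although nothing has changed.

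The affected quantity is the outcome of objective 2.1, and Section 4.3 promises a conclusion on long-term decline after ARI and SARI. Sections 3.1.4 and 7.5.1 give each response 0 to 3 points and set the frailty threshold at 3, so a single item can matter for an individual. Once data have been collected on mismatched forms, artefact and true change cannot be separated on these items.

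**Working it through.** **Step 1. The two forms side by side.**

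| Item | 4b (enrolment) | 4f (follow-up) |
|---|---|---|
| Walking, main question | item 22: aid not mentioned | item 18: cane or walker allowed |
| Walking, sub-item | item 24: *can't* | item 20: *don't* |
| Light housework, sub-item | item 27: *can't* | item 23: *don't* |
| Bathing, sub-item | item 30: *can't* | item 26: *don't* |
| Shopping and money, sub-items | items 18, 21: *don't* | items 14, 17: *don't* |
| Self-rated health, top code | item 4: very good or excellent | item 1: very good |

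Form 4b mixes *can't* and *don't* within itself, which suggests a drafting slip.

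**Step 2. Which comparisons cross the two wordings.** The protocol does not name the form used for the six-monthly repeats.

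- If the repeats use 4f, the change from enrolment to the first repeat crosses wordings and later changes do not. A matched pair is mixed when one member has only an enrolment score and the other has a repeat.
- If the repeats use 4b, the six-monthly changes share one wording. Every change from a reference score to the post-illness 4f interview then crosses wordings, in cases and controls alike.

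**Step 3. The plan's own figure (Section 7.1.5).** Inputs: means 4 and 5 (difference 1), SD 3, correlation 0.2, type I error 0.05 (taken as two-sided), power 80%. Taking SD 3 per measurement, the SD of the difference is 3 × √(2 × (1 − 0.2)) = 3.795. The paired t test then needs 115 pairs, with power 80.0% at 115. This reproduces the stated figure.

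**Step 4. Size on the walking item (assumed inputs).** The protocol gives neither the share of aid users nor the points for this item. Let *s* be the share who switch from yes to no only because of the wording, and *p* the points lost.

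- Mean within-person shift = −*s* × *p*.
- *s* = 1%, *p* = 1: −0.01 points.
- *s* = 10%, *p* = 3: −0.30 points.

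**Step 5. The matched comparison.** Let *s* in each group count those whose change spans 4b to 4f and who switch. The net shift in the case-control difference is −*p* × (*s* in cases − *s* in controls).

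- Equal shares: shift 0, difference 1, power 80.0%.
- Share 2 percentage points higher in cases, *p* = 1: difference 1 − 0.02 = 0.98, power 78.4%.
- Share 5 percentage points higher in cases, *p* = 3: difference 1 − 0.15 = 0.85, power 66.3%.
- The same imbalances in the other direction would inflate the difference to 1.02 and 1.15.

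**The case against.** The strongest reply is that the design of objective 2.1 already protects the comparison. Case and control are matched on the latest score and interviewed at the same time, so a shift common to both drops out. Interviews start in January 2016, more than six months after enrolment in June 2015, so most participants should have a six-month score and mixed pairs should be uncommon. This stands, and it confines the problem in the matched analysis to mixed pairs and to unequal shares of aid users. It does not protect uncontrolled within-person change from a 4b score to a 4f score.

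It can also be said that no scoring key is given. Both forms go on to ask whether the participant gets help with walking. If points need both difficulty and help, a cane user who walks unaided by others may score nothing on either form. Section 7.3 excludes people with disabilities that affect self-swabbing or interview, which may remove some aid users. The fielded forms are in Thai, and only the English is shown. These points stand too: they make the size unknown, possibly zero for some people.

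A reader might infer more: that measured change is biased towards improvement overall, and that decline after ARI or SARI is hidden. The protocol does not support this. The move from *can't* to *don't* could draw more answers attributing inactivity to health at follow-up, which would look like worsening. A reader might also count the self-rated health stem, whose option *poor* has no matching code, as a source of spurious change. That mismatch is the same on both forms, so it cannot create a difference between them.

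**Conclusion.** The wording differences are real and conflict with the plan to re-take one instrument. Within-person change from a 4b score to a 4f score can include a wording artefact. For aid users on the walking item it would look like improvement; across all altered items neither the net direction nor the size can be derived.

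The 0.01 to 0.30 points rest entirely on an assumed 1% to 10% switching and 1 to 3 points for the item. The matched comparison is largely unaffected; power falls to between 78.4% and 66.3% only under the assumed 2 to 5 percentage-point excess of switching in cases. The 115-pair calculation does not depend on this point. The matter concerns a secondary objective, and it is cheap to correct.

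**What to change.** - Use one identical item text and response list on 4b and 4f: the same statement on walking aids, the same sub-item wording and the same self-rated health codes.
- Separately, make the self-rated health codes match the options read out, on both forms.
- State which form is used for the six-monthly repeats.
- For data already collected on the existing 4b, compute change, and match cases to controls, only on scores from the same wording. Alternatively, run a sensitivity analysis without the altered items.

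The cost is an edit to the electronic forms and one matching rule, with no extra visits. The downside is that some enrolment scores cannot serve as the reference for change, so participants without a same-wording score cannot enter the matched analysis until they have one.

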**END OF QUESTIONNAIRE**

**4g. Outcomes and Costs of ARI/SARI Questionnaire (For Health Volunteer)**

|                             |                                                                                       |                                                          |                                                   |
|-----------------------------|---------------------------------------------------------------------------------------|----------------------------------------------------------|---------------------------------------------------|
| Study identification number |                                                                                       |                                                          |                                                   |
| Date                        | (DD/MM/YY)                                                                            |                                                          |                                                   |
| HN number                   |                                                                                       |                                                          |                                                   |
| Type of Weekly contact      | Please choose:    In Person        Phone                                              |                                                          |                                                   |
| No.                  | Questions and filters (variable names)                                         | Coding categories                                 | Skip                                       |
| 1                           | Do you work? (for example, in the agricultural fields, run business, other job, etc.) | 1 Yes
2 No
77 Do not know
99 Declined to answer | If answered No or Do not know, skip to question 3 |
| 2                           | How many days of work did you miss because of your illness?                           | _____ days                                               |                                                   |
| 3                           | Does your primary caregiver earn money in addition to taking care of you?             | 1 Yes
2 No
77 Do not know
99 Declined to answer | If No, skip to question 8                         |
| 4                           | How many days was your caregiver unable to work because they were taking care of you? | _____ days                                               |                                                   |
| 5                           | How much does the primary caretaker earn per day?                                     | Average: _____Thai baht / day                            |                                                   |

|    |                                                                                                               |                                                          |                            |
|----|---------------------------------------------------------------------------------------------------------------|----------------------------------------------------------|----------------------------|
|    |                                                                                                               |                                                          |                            |
| 6  | Did the primary caregiver lose any income by looking after you while you were sick?                           | 1 Yes
2 No
77 Do not know
99 Declined to answer | If No, skip to question 9  |
| 7  | How much?                                                                                                     | _____ Thai baht                                          |                            |
| 8  | Is there a risk of your caregiver losing their job for staying home to look after you?                        | 1 Yes
2 No
77 Do not know
99 Declined to answer |                            |
| 9  | Did anyone else lose any income by looking after you?                                                         | 1 Yes
2 No
77 Do not know
99 Declined to answer | If No, skip to question 14 |
| 10 | How many days was the other household member who looked after you not able to work because of caring for you? | _____ days                                               |                            |
| 11 | How much does the other household member who looks after you earn per day?                                    | Average: _____ Thai baht / day                           |                            |
| 12 | Did the other household member lose any income by looking after you while you were sick?                      | 1 Yes
2 No
77 Do not know
99 Declined to answer | If No, skip to question 14 |

|                                                                                         |                                                                                                                                                    |                                                          |                                     |
|-----------------------------------------------------------------------------------------|----------------------------------------------------------------------------------------------------------------------------------------------------|----------------------------------------------------------|-------------------------------------|
| 13                                                                                      | How much?                                                                                                                                          | _____ Thai baht                                          |                                     |
| 14                                                                                      | Does your family need to give up purchasing something necessary in order to pay for treatment while you were sick? For example, food?              | 1 Yes
2 No
77 Do not know
99 Declined to answer |                                     |
| 15                                                                                      | How many days were there from the beginning of the illness until you recovered?                                                                    | _____ days                                               |                                     |
| 16                                                                                      | During this whole illness, how many times did you see a medical doctor or a nurse for your illness?
Please count all times until you recovered. | _____ times                                              |                                     |
| Please indicate the mechanisms you used to pay for the expenses caused by your illness? |                                                                                                                                                    |                                                          |                                     |
| 17                                                                                      | Government health plan                                                                                                                             | 1 Yes
2 No                                            |                                     |
| 18                                                                                      | Civil servant medical benefit scheme                                                                                                               | 1 Yes
2 No                                            |                                     |
| 19                                                                                      | Health Insurance you purchased yourself (private insurance)                                                                                        | 1 Yes
2 No                                            |                                     |
| 20                                                                                      | Out of pocket                                                                                                                                      | 1 Yes
2 No                                            |                                     |
| 21                                                                                      | Borrowed money                                                                                                                                     | 1 Yes
2 No                                            | If No,
skip to
question
23 |
| 22                                                                                      | What was the interest rate?                                                                                                                        | _____ %                                                  |                                     |

|    |                                                                                                                                                           |                                                                                         |                                     |
|----|-----------------------------------------------------------------------------------------------------------------------------------------------------------|-----------------------------------------------------------------------------------------|-------------------------------------|
| 23 | Other sources                                                                                                                                             | 1 Yes

2 No                                                                       | If No,
skip to
question
25 |
| 24 | Specify                                                                                                                                                   | _____                                                                                   |                                     |
| 25 | How much money did you spend on transportation fees to and from all visits to hospitals and clinics?                                                      | _____ Thai baht                                                                         |                                     |
| 26 | How much money did you spend on all medications not provided by the hospital or clinic (including herbals) and treatments (including traditional healers) | _____ Thai baht                                                                         |                                     |
| 27 | Which public health-centers/hospitals did you visit for your illness?                                                                                     | Please List:

1 _____

2 _____

3 _____

4 _____

5 _____ |                                     |
| 28 | Did you visit any private health centers during your illness?                                                                                             | 1 Yes

2 No

77 Do Not Know

99 Declined to answer                    |                                     |
| 29 | How much money did you spend on the total treatment of your illness at the private health centers? (Including all laboratory and                          | _____ Thai baht                                                                         |                                     |

|    |                                                                                                                                                                                                                |                |  |
|----|----------------------------------------------------------------------------------------------------------------------------------------------------------------------------------------------------------------|----------------|--|
|    | examination tests, clinician fees, hospital fees, medication fees)                                                                                                                                             |                |  |
| 30 | How much money did your insurance spend on the total treatment of your illness at the private health centers? (including all laboratory and examination tests, clinician fees, hospital fees, medication fees) | _____Thai baht |  |

\_\_\_\_\_END\_\_\_\_\_

**4h. Screening and Enrollment Questionnaire for Immunogenicity study****Questionnaire 1: Personal Data to link in a separate database**

|                                                      |                   |                                                           |
|------------------------------------------------------|-------------------|-----------------------------------------------------------|
| Name of selected participant                         |                   |                                                           |
| Participant Study ID Number                          |                   |                                                           |
| Name of study team member                            |                   |                                                           |
| District Hospital                                    | Circle one:       | That Phanom                      Plapak                   |
| Date                                                 | (DD/MM/YY)        |                                                           |
| Participant's Home phone number                      |                   |                                                           |
| Participant's Cell phone number                      |                   |                                                           |
| Is there a caregiver?                                | 1 Yes

2 No | Caregiver's name:                                         |
| Phone number for caregiver?                          |                   | Circle the number that we should use for the weekly call. |
| Participant's age (years)                            |                   |                                                           |
| Have you lived in Nakhon Phanom since Songkran 2014? | 1 Yes

2 No |                                                           |

**Questionnaire 2: Screening form for influenza vaccine coverage and vaccination determinant for elderly age 65 years and over**  
